#### FICare recruitment

Within 72 h of admission to the level II NICU, nurses will inform mothers about the study. If interested, a FICare super-user (a nurse specially trained in the FICare model) will screen mothers for eligibility, answer questions about the study, obtain informed consent, and administer the baseline questionnaire. As this is a cRCT, infants of mothers at the intervention sites who do not wish to participate in the study will receive the same hospital care as infants whose mothers are participating in the study. The present study will be nested within the larger FICare clinical trial (Fig. 3).

**Fig. 3 Fig3:**
[figure not shown]
Situation of present study within larger FICare clustered randomised control trial

### Quantitative phase

#### Procedures

Online questionnaires will be administered to mothers at two time points in the study (Table 1). The first set of questionnaires will be administered at enrolment; the second set about 24 h before the infant is discharged from the NICU.

**Table 1 Tab1:** Outcome measures and potential covariates with breastfeeding self-efficacy and breastfeeding outcomes

Measure	Time point	Description
Primary outcome		
Modified Breastfeeding Self-Efficacy Scale - Short Form [20]	Baseline; Discharge	18-item scale validated for mothers of ill and/or preterm infants. Assesses a mother’s confidence in her ability to breastfeed. Internal consistency (0.88) is high.
Secondary outcome		
Breastmilk feeding	Baseline; Discharge	Labbok and Krasovek [41] classification system, modified to include additives and fortification. 24-h maternal recall.
Co-variates and potential confounders		
Parental Stressor Scale: NICU [62]	Baseline; Discharge	50-item scale that captures parental perceptions of stress in the NICU: (1) sights and sounds; (2) appearance and behaviour of the infant; (3) impact on the parental role and relationship with the infant; and (4) parental relationship and communications with staff. Internal consistency (0.89 to 0.94 for the total scale) and test-retest (0.87) reliabilities are high. *Potential confounding:* Decreasing maternal anxiety and stress may have a physiologic impact on breastmilk production [63, 64].
Edinburgh Postnatal Depression Scale [65]	Baseline; Discharge	The most commonly used pre- and post-natal depression screener validated for mothers. Consists of 10 items and has a sensitivity of 0.86 and specificity of 0.78, with a positive predictive value of 73%. *Potential confounding:* Successful breastfeeding is predictive of lower maternal depressive symptomology. Depressive symptoms may be predictive of reduced breastfeeding rates [66].
State-Trait Anxiety Inventory [67]^a^	Baseline; Discharge	40-item scale that captures dispositional/trait anxiety (20 items) and current state anxiety (20 items). Internal consistency (0.86 to 0.95) and test-retest (0.73 to 0.86) reliabilities are high. Scores on the STAI and PSS: NICU are correlated [62]. *Potential confounding:* Mothers who demonstrate high rates of anxiety or depressive symptomology routinely have lower breastfeeding rates than mothers that do not [66].
Perceived Maternal Parenting Self-Efficacy scale [68]	Baseline; Discharge	20-item measure of parenting self-efficacy validated for mothers of preterm infants. Captures maternal perceptions of ability to (1) give basic care; (2) elicit change in infant behaviour; (3) recognize infant behaviour; and (4) judge interactions with her infant. Exploratory factor analysis confirms four factors; internal consistency (0.91) and test-retest (0.96) reliabilities are high. *Potential confounding:* Concurrent validity between general self-efficacy and BSES-SF [22].

^a^At admission, both State and Trait forms are completed; at discharge only State form is completed. Adapted from Benzies et al. [30]

#### Measurement

Breastfeeding self-efficacy will be measured using the modified Breastfeeding Self-efficacy Scale – short form (BSES-SF; Table 1) for mothers of ill and preterm infants [20]. The BSES-SF will only be administered to mothers who are breastfeeding, expressing their own breastmilk, attempting to breastfeed, or are planning to breastfeed. Mothers who have weaned or are not planning to breastfeed will not complete the BSES-SF. However, infant feeding rates will be captured for all infants in the study. BSES-SF data will be assessed quarterly throughout the quantitative data collection period and will inform purposive sampling for the qualitative phase of the study. The remaining quantitative data will be assessed upon completion of quantitative data collection and completion of qualitative data analysis.

The Labbok and Krasovek classification system [41] will be used to assess infant feeding rates at admission and discharge (Table 1). Maternal recall is frequently used as an effective method to collect infant feeding data [42]. Maternal recall will be used to assess infant feeding over the previous 24 h and will be classified as:i.Exclusive breastmilk feeding – 100% of feeds were breastmilk (including expressed breastmilk, donor human milk and additives)ii.Mostly breastmilk – 75% of feeds were breastmilk (including expressed breastmilk, donor human milk and additives)iii.Partial breastmilk feeding - 50% of feeds were breastmilk (including expressed breastmilk, donor human milk and additives)iv.Minimal breastmilk - 25% of feeds were breastmilk (including expressed breastmilk, donor human milk and additives).v.No breastmilk feeding – baby is not receiving any breastmilkvi.nil per os (NPO) or nothing by mouth

The infant feeding questions will be predicated by i) is your baby receiving any human donor milk, and ii) is your baby receiving any additives to your breastmilk to help them grow?

#### Data management

We will collect data electronically and data will be stored on secure servers. Quantitative data will be managed as per Benzies et al. [30]. Upon completion of analysis, we will store data with the PolicyWise Secondary Analysis to Generate Evidence (SAGE; formerly the Child Data Centre of Alberta) database. This will help to facilitate data access by other qualified researchers.

#### Data analysis

Statistical analysis of the quantitative results will be performed using Stata Data Analysis and Statistical Software. The primary outcome of the statistical analysis is to determine if a difference exists in: i) breastfeeding self-efficacy scores (BSES-SF) and ii) breastmilk feeding rates, between the control and intervention groups. Results from the BSES-SF will be treated as continuous data whereas results from breastmilk feeding rates will be treated as categorical data [20, 43]. Characteristics of participants and scores on scales will be presented as descriptive statistics (means, frequencies, and percentages). We will use an omnibus test (Hotelling’s t-tests and Chi square) to assess for baseline differences between intervention and control groups on socio-demographic and health characteristics, breastfeeding self-efficacy, and breastmilk feeding rates.

To test if there is a difference in breastfeeding self-efficacy and breastmilk feeding rates between the intervention and control groups, we will use Hierarchical Linear Modeling (HLM; also known as multilevel modeling or mixed-effect modeling) and Hierarchical General Linear Modeling (HLGM), respectively. This study is nested in a larger cRCT and there is a potential for variance in care delivery at each of the NICU sites. As such, there are multiple levels of data that need to be considered to accurately assess the effectiveness of the intervention on breastfeeding self-efficacy and breastmilk feeding rates. By simultaneously investigating the relationships between the different levels of data, HLM and HGLM analysis can account for variance among variables at different levels [44]. The HLM approach will allow for the two observations (admission and discharge from the NICU) by treating each participant’s breastfeeding self-efficacy score and breastmilk feeding rate at each assessment point as single data points [44]. There will be two levels of analysis in the data: Level 1 will refer to the outcome variables of breastfeeding self-efficacy and breastmilk feeding rates; while Level 2 will be the maternal or subject effect. We will enter the subject effect into the model as a random effect to capture within and between-subject variation [44]. The group effect of intervention/control will be entered as fixed effect to determine if the intervention is effective.

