### FICare cluster randomized controlled trial

All level II NICUs in the province of Alberta, Canada (*N* = 10) will be randomized into a standard care control group (*n* = 5) or an intervention group (*n* = 5). Each intervention site will have specially trained registered nurse super-users who are responsible to recruit participants, deliver the intervention, and collect data. To ensure intervention fidelity, we will conduct site visits four times per year to assess adherence and compliance with the intervention components. We will also monitor for activities (e.g. policy changes, guidelines, unit practices) that may influence implementation of FICare.

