#### FICare sample size

We based sample size estimates on the primary outcome, length of stay. Due to an anticipated skewed distribution for length of stay, we used a natural logarithm transformation to calculate sample size [40]. To achieve a power of 0.80, we need to recruit 181 mothers into each group for the primary outcome of length of stay; and 211 to achieve a power of 0.9. In 2014, there were 1030 moderate and late preterm infants admitted to a level II NICU in Alberta. To account for a response rate of 80% [36], attrition, and infants with a length of stay of ≤5 days (6.08%), we will approach 824 potential participants over the 30-month recruitment period. This will also ensure that the sample size, 330 per group, is sufficient to assess secondary outcomes and to provide the qualitative sample for the study.

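### The baseline comparison of arms uses tests that treat mothers as independent although ten NICUs are randomised, so its false-positive rate exceeds the nominal 5%

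*Protocol article*

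**What the plan says.** The protocol article, under FICare cluster randomized controlled trial, states that all ten level II NICUs in the province "will be randomized into a standard care control group" of five units or an intervention group of five. The unit of randomisation is the NICU.

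Under Quantitative phase, Data analysis, the baseline comparison is specified as follows: "We will use an omnibus test (Hotelling’s t-tests and Chi square) to assess for baseline differences between intervention and control groups". It covers the mothers' background and health, the self-efficacy score and infant feeding. No unit of analysis and no adjustment for NICU is given for these tests. The next paragraph, on the outcome models, says that "there is a potential for variance in care delivery at each of the NICU sites".

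Under FICare recruitment, a trained nurse at the unit will "screen mothers for eligibility, answer questions about the study, obtain informed consent, and administer the baseline questionnaire".

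The numbers come from FICare sample size: "This will also ensure that the sample size, 330 per group, is sufficient to assess secondary outcomes", and, for the main trial's primary outcome, "we need to recruit 181 mothers into each group for the primary outcome of length of stay; and 211 to achieve a power of 0.9".

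**The concern.** When hospitals are randomised, a chance difference between the arms reflects both how mothers vary and how the five hospitals in each arm vary. Mothers in one NICU share a catchment, a case mix and unit practices. Hotelling's test and chi-square, as normally computed, measure the arm difference against variation between mothers only. Their p-values are then too small.

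A baseline comparison has a real use in this design. Mothers are approached and consented by staff at the units, and at the intervention sites by nurses trained to deliver the intervention, so the arms could differ because different mothers were recruited. A test that also responds to ordinary differences between ten hospitals cannot separate the two. A significant result could be reported as imbalance when nothing beyond chance had happened.

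This is separate from the outcome models: changing their levels would not alter the baseline tests.

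**Working it through.** **Inputs from the article.** Ten NICUs, five per arm. Planned size 330 per group; minimum for length of stay 181 per group (power 0.80).

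**Reproducing the planned size.** 824 approached × 0.80 response ÷ 2 arms = 329.6, or 330. Deducting the 6.08% short stays as well gives 824 × 0.80 × (1 − 0.0608) ÷ 2 = 309.6, about 310. With equal sites, 330 ÷ 5 = 66 mothers per NICU and 181 ÷ 5 = 36.2.

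**Assumptions, because the article gives none of these.** Two-sided 5% level; ICC 0.01 to 0.10; one to eight variables; equal site sizes unless stated; no true difference between arms.

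**One variable.** Design effect DE = 1 + (m − 1) × ICC, where m is mothers per NICU. Actual size = 2 × [1 − Φ(1.96 ÷ √DE)]. For m = 66 and ICC 0.05, DE = 1 + 65 × 0.05 = 4.25, 1.96 ÷ √4.25 = 0.951, and the size is 34.2%.

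| ICC | DE, m = 66 | Size | DE, m = 36.2 | Size |
|---|---|---|---|---|
| 0.01 | 1.65 | 12.7% | 1.35 | 9.2% |
| 0.02 | 2.30 | 19.6% | 1.70 | 13.3% |
| 0.05 | 4.25 | 34.2% | 2.76 | 23.8% |
| 0.10 | 7.50 | 47.4% | 4.52 | 35.7% |

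For one variable the size reaches 50% when DE = (1.96 ÷ 0.6745)² = 8.44. That is ICC = 7.44 ÷ 65 = 0.115 at 66 per NICU, or 7.44 ÷ 35.2 = 0.21 at 36.2.

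**Hotelling's test, simulated on individual mothers** (2,000 runs per cell, correlation 0.3 between variables):

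| Per arm | Variables | ICC 0.01 | 0.02 | 0.05 | 0.10 |
|---|---|---|---|---|---|
| 330 | 3 | 19% | 34% | 62% | 78% |
| 330 | 5 | 25% | 45% | 76% | 91% |
| 330 | 8 | 30% | 57% | 89% | 98% |
| 181 | 3 | 13% | 21% | 41% | 61% |
| 181 | 5 | 14% | 27% | 56% | 80% |
| 181 | 8 | 20% | 33% | 70% | 91% |

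With unequal site sizes (assumed coefficient of variation 0.6), five variables and 330 per arm, the rates are 32%, 54%, 82% and 95%.

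**Chi-square, simulated on individual mothers** (4,000 runs per cell, 330 per arm, ICC on the scale of the categorical variable): 13%, 19%, 34% and 47% for a binary variable; 21%, 39%, 69% and 88% for five categories with assumed proportions. The scale of the ICC matters. An ICC of 0.05 on an underlying normal variable cut at 30% is only about 0.029 on the binary scale, which gives DE = 1 + 65 × 0.029 = 2.9 and a size of about 25%.

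**Checks.** At ICC 0 all these tests run at about 5%. A t-test on the ten NICU means (8 degrees of freedom, one variable) holds its size at 5.0% to 5.2% for ICC 0 to 0.10.

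**The case against.** The article never says that the tests are run on individual mothers. That is an inference, but the natural one. The preceding sentence concerns participants' characteristics, and a chi-square on feeding categories needs counts of mothers. A Hotelling test on ten NICU means would have 8 error degrees of freedom and could not take more than eight variables.

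The stronger objections concern consequence:

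- **No decision rests on the test.** Table 1 names covariates and potential confounders in advance, and outcomes are tested in separate models. A reader might infer that spurious flags will drive covariate adjustment or bias the estimated effect. The plan contains no such step. This objection stands and limits the point.
- **Descriptive statistics are already planned.** It would therefore be too much to call the tests the only view of baseline balance, although the sentence on descriptive statistics does not say that they will be shown by arm or by NICU.
- **66 per NICU may be too high.** Mothers not planning to breastfeed do not complete the self-efficacy scale, and Hotelling's test needs complete sets of values. The rows for 181 per arm address this; the rates are lower but still above 5%.
- **Pooling variables is not itself the fault.** If five independent variables were each tested at a true size of 34.2%, at least one would be flagged in 1 − 0.658⁵ = 88% of trials, against 76% for Hotelling's test on all five. Ignoring NICU is the error.

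**Conclusion.** The point holds. The named tests, in standard form, do not fit a trial that randomises ten NICUs, and their false-positive rate exceeds 5% at any non-trivial ICC. Under the stated assumptions, with 66 per NICU, it is about 13% to 47% for one continuous or binary variable and about 25% to 91% for Hotelling's test on five. At an ICC of about 0.05 it passes 50% with three or more variables (five or more at 181 per arm).

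A reader might infer that the tests will usually declare the arms different. The documents do not support that, because they give neither an ICC nor the number of variables. At ICC 0.01 no rate computed here reaches 50%. With equal sites, neither a single continuous variable nor a binary chi-square reaches 50% at any ICC up to 0.10.

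The consequence is limited to a possibly misleading statement about baseline imbalance. The effect estimates do not depend on it.

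**What to change.** In Quantitative phase, Data analysis, replace the sentence on Hotelling's test and chi-square. Describe baseline characteristics by arm, with standardised differences, and by NICU, so that an arm difference can be read against the spread between units.

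If a test for recruitment differences is wanted, make it a NICU-level test. One choice is to permute the ten NICUs over the allocations that the randomisation allowed. If unrestricted, there are 10! ÷ (5! × 5!) = 252, with a smallest two-sided p-value of 2 ÷ 252 = 0.008. The other is a test on NICU means. State that adjustment covariates are fixed beforehand and are not chosen from this comparison.

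The cost is a change of wording and, for the permutation, a short script. No new data, participants or staff are needed. The drawback is that a test on ten units has low sensitivity, so a non-significant result would not show that recruitment was comparable. The descriptive display should carry most of the weight.

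### The planned two-level model leaves out the randomised NICU, so the group effect is tested against the wrong error term and its false-positive rate can be well above 5%

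*Protocol article*

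**What the plan says.** Under *FICare cluster randomized controlled trial*, all ten level II NICUs in Alberta "will be randomized into a standard care control group" of five units or an intervention group of five. The NICU is therefore the unit of randomisation.

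The *Data analysis* section of the quantitative phase assigns HLM to breastfeeding self-efficacy and its generalised counterpart to breastmilk feeding. Part of the reason given is that "there is a potential for variance in care delivery at each of the NICU sites". The section then specifies the model:

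- "There will be two levels of analysis in the data".
- Level 1 is the two outcome variables, observed at admission and discharge; "Level 2 will be the maternal or subject effect".
- "We will enter the subject effect into the model as a random effect".
- Group (intervention or control) is a fixed effect, and that effect decides whether the intervention works.

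No NICU random effect, third level, cluster-robust variance or cluster-level degrees of freedom appears anywhere in the article.

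**The concern.** A random effect for the mother handles the correlation between her own two measurements. It does nothing for the correlation between different mothers in the same NICU. Arm is constant within a NICU, so any difference between NICUs feeds into the group contrast. Its standard error has to reflect variation between the five NICUs within each arm. The model as written uses variation between mothers and treats several hundred of them as independent.

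The article itself makes NICU differences plausible. *FICare context – Level II NICUs* says that visitation models vary, that open and closed wards are mixed, and that five units plan to change to single rooms during the study.

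At stake is the test of both quantitative outcomes. A chance difference between two sets of five NICUs could be reported as an effect of FICare, and the Discussion says an effective result could change how level II NICUs deliver care.

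**Working it through.** **Inputs from the article**

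- Ten NICUs, five per arm (*FICare cluster randomized controlled trial*).
- 330 mothers per group for secondary outcomes; 181 per group as the 80%-power figure for length of stay (*FICare sample size*).
- The plan's 330 reproduces: 824 approached × 0.80 response ÷ 2 = 329.6.
- Mothers per NICU: 330/5 = 66. As a low case, 181/5 = 36.2. A low case is needed because mothers who have weaned or do not plan to breastfeed skip the BSES-SF (*Measurement*).

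**Assumptions, because the article does not give them**

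- Two-sided nominal 5% test; equal NICU sizes.
- ICC from 0.001 to 0.05.

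**Step 1: one time point, continuous outcome**

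Design effect: DE = 1 + (m − 1) × ICC. Actual error of a nominal 5% test that ignores the NICU: 2 × [1 − Φ(1.96/√DE)].

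Example: m = 66 and ICC = 0.02 give DE = 1 + 65 × 0.02 = 2.30; 1.96/√2.30 = 1.292; error = 19.6%.

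| Mothers per NICU | ICC | DE | Actual error |
|---|---|---|---|
| 66 | 0.001 | 1.07 | 5.8% |
| 66 | 0.005 | 1.33 | 8.9% |
| 66 | 0.01 | 1.65 | 12.7% |
| 66 | 0.02 | 2.30 | 19.6% |
| 66 | 0.05 | 4.25 | 34.2% |
| 36 | 0.01 | 1.35 | 9.2% |
| 36 | 0.02 | 1.70 | 13.3% |
| 36 | 0.05 | 2.76 | 23.8% |

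Simulation of 20,000 null trials per setting agrees: 12.5%, 19.9% and 34.2% at 66 per NICU for ICC 0.01, 0.02 and 0.05. In the same simulations a t-test on the ten NICU means (8 df) rejected in 4.9% to 5.2% of trials, over ICC 0 to 0.05 and both cluster sizes.

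**Step 2: group main effect pooled over admission and discharge**

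Further assumption: variation between mothers is half of the total variance of a single observation. Averaging two observations shrinks the residual but not the NICU component, so the ICC of the mother's mean is ICC/[ICC + 0.5 + (0.5 − ICC)/2].

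- ICC 0.02: 0.02/0.76 = 0.0263; DE = 1 + 65 × 0.0263 = 2.71; error 23.4% (simulated 23.7%).
- ICC 0.05: 0.05/0.775 = 0.0645; DE = 5.19; error 39.0% (simulated 39.5%).

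**Step 3: group-by-time contrast**

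A constant NICU shift cancels in each mother's change score. The simulated error is then 4.6% to 5.3%, so there is no inflation. If change also varies by NICU, the ICC of the change score is V/(0.5 − ICC), where V is the NICU-by-time variance as a share of the total and ICC is the constant NICU share.

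| Constant NICU share | V | ICC of change | DE (m = 66) | Error, formula | Error, simulated |
|---|---|---|---|---|---|
| 0.01 | 0.005 | 0.0102 | 1.66 | 12.9% | 13.3% |
| 0.04 | 0.01 | 0.0217 | 2.41 | 20.7% | 21.0% |
| 0.05 | 0.02 | 0.0444 | 3.89 | 32.0% | 32.6% |

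**The case against.** **The article is a summary, and a fuller analysis plan may add the NICU.** This would be a good answer if the article only said that a mixed model will be used. It goes further: it counts the levels, names them, and names the random and fixed effects. An analyst who follows it fits a model without the NICU. The general remark that multilevel models handle variance at different levels does not help, because a model handles only the levels it contains.

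**The ICC may be very small.** All ten units are in one province and formally support mother's own milk as first choice. This stands as a limit on size: at ICC 0.001 the error is only 5.8%.

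**Objective i is about change from admission to discharge, and a change contrast need not be inflated.** This also stands in part. If NICUs differ only by a constant shift, a group-by-time test is sound. But the *Data analysis* section names a group effect and no interaction. Change itself could also vary by NICU if care delivery does.

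**Two stronger readings should be resisted.** A reader might infer that NICU variation is wholly confounded with arm, so that no valid test exists. That is not so: ten NICUs give 9 between-NICU degrees of freedom, and 8 of them lie within arms and supply a valid error term. A reader might also apply the percentages above to breastmilk feeding. They were computed for a continuous outcome only; for the categorical outcome the direction is the same but the size was not calculated.

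**Conclusion.** The point holds as a defect of stated method. The specified model omits the randomised unit and contradicts its own rationale, so the group effect lacks a valid error term.

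The size is conditional. At 66 mothers per NICU, the error for a continuous outcome at one time point runs from about 5.8% (ICC 0.001) to 34.2% (ICC 0.05). At 36 per NICU it is about 9.2% to 23.8% for ICC 0.01 to 0.05. The main effect pooled over two time points is somewhat worse, about 24% at ICC 0.02 and 40% at 0.05. A group-by-time contrast ranges from near 5% to about 33%, depending on whether change varies by NICU.

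All of this assumes a two-sided 5% test, equal NICU sizes and the ICC range shown. A reader might conclude that the error is certainly far above 5%. The documents do not support that, because they give no ICC. They do support the conclusion that it can be, and that the plan contains nothing to prevent it.

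**What to change.** In the quantitative *Data analysis* section, replace the two levels with three: time within mother within NICU. Include a random intercept for NICU, and a NICU-by-time random effect if the contrast of interest is change. State which contrast is tested.

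- **BSES-SF:** use Kenward-Roger or Satterthwaite degrees of freedom, suited to ten clusters. A t-test on NICU-level summaries with 8 df is an acceptable alternative.
- **Breastmilk feeding:** use NICU-level summaries with a t-test on 8 df. The Kenward-Roger and Satterthwaite corrections belong to linear mixed models and do not carry over to a categorical outcome.

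The change needs revised text and a few lines of code, and no new data. The cost is precision: confidence intervals widen and the effective sample size falls. By the design effects above, 330 per group is worth about 330/2.30 = 143 independent mothers at ICC 0.02, or 330/4.25 = 78 at ICC 0.05. The statement that 330 per group suffices for secondary outcomes should be read again in that light.

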### Study aim

This study is nested within a larger cluster randomized control trial (cRCT) assessing multiple outcomes of a Family Integrated Care (FICare) for moderate and late preterm infants in level II NICUs [30]. The primary outcome of the FICare cRCT is to evaluate the effect of FICare on length of stay in the level II NICU. The aim of the *present* study is to determine if FICare improves maternal breastfeeding self-efficacy and resultant breastmilk feeding rates in mothers of moderate and late preterm infants who were admitted to a level II NICU. The specific objectives are:i.To determine if FICare is effective in improving breastfeeding self-efficacy in mothers of moderate and late preterm infants between admission to and discharge from a level II NICU.ii.To determine if FICare is effective in increasing breastmilk feeding rates in mothers of moderate and late preterm infants at discharge from the NICU.iii.To explore maternal experiences with infant feeding while admitted to the NICU.iv.To determine if or how maternal experiences with infant feeding work to inform maternal breastmilk feeding rates while in the FICare NICU environment.

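### The fixed group effect over stacked admission and discharge values does not estimate the improvement (objective i) or the discharge difference (objective ii) that the study sets out to test

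*Protocol article*

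**What the plan says.** Objective i, under Study aim, concerns improvement in breastfeeding self-efficacy "between admission to and discharge from a level II NICU". Objective ii concerns breastmilk feeding rates at discharge.

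Under Procedures, the two measurements are timed as follows: "The first set of questionnaires will be administered at enrolment; the second set about 24 h before the infant is discharged from the NICU".

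The quantitative Data analysis section makes three linked choices:

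- Both time points are outcomes. The model treats each mother's self-efficacy "score and breastmilk feeding rate at each assessment point as single data points".
- There are two levels, observation and mother: "We will enter the subject effect into the model as a random effect to capture within and between-subject variation".
- The effectiveness decision rests on one term: "The group effect of intervention/control will be entered as fixed effect to determine if the intervention is effective".

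The section names no time term, group-by-time term or adjustment for the admission value. It plans tests for baseline differences between arms but does not say how a difference would be handled. It mentions variation in care between NICU sites, but the only random effect that it names is the subject effect.

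**The concern.** The admission score is taken at enrolment, before the intervention has had much time to act. If it enters as an outcome, a group main effect mixes a difference that should be near zero with the discharge difference that matters. The resulting number is neither the between-arm difference in change nor the difference at discharge.

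Three consequences follow. A real benefit is reported as smaller than it is. A moderate benefit may be missed. And the admission difference between arms becomes part of the reported effect, which is a real risk with only 10 randomised sites. The BSES-SF is the primary outcome of this nested study in Table 1, so its main conclusion is affected.

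**Working it through.** **Plan's own figures.** The article gives no effect size, SD, correlation or power for the BSES-SF. Its powered figures are for another outcome: "To achieve a power of 0.80, we need to recruit 181 mothers into each group for the primary outcome of length of stay". They cannot be rebuilt from what is given and are not used here. The planned 330 per group does follow from the FICare sample size section: 824 × 0.80 / 2 = 329.6. It is used below as n.

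**Assumptions not in the article.** Two-sided alpha 0.05; equal SD (set to 1) at both time points; within-mother correlation r from 0 to 0.7; complete pairs; site clustering ignored.

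**Step 1: what the coefficient estimates.** Let D0 and D1 be the between-arm differences at admission and discharge. With complete pairs and a random intercept, the group coefficient is (D0 + D1)/2. Objective i needs D1 − D0, or D1 adjusted for the admission value. Objective ii needs D1. If D0 = 0 in expectation and D1 = d, the coefficient is d/2. If D0 is not zero, D0/2 enters it. A time main effect shifts both arms equally and leaves the group coefficient unchanged.

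A small simulation (40 replicates, n = 330, r = 0.5, d = 0.189) gave a mean group coefficient of 0.086, with or without a time main effect. The expected value is 0.189/2 = 0.0945. The simulation standard error is √(0.75 × 2/330)/√40 = 0.0674/6.32 = 0.011, so the two agree.

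**Step 2: precision.** Each variance below is multiplied by 2/n.

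| Analysis | Estimates | Variance factor |
|---|---|---|
| Group main effect, stacked rows | d/2 | (1 + r)/2 |
| Discharge adjusted for admission | d | 1 − r² |
| Group-by-time (change) | d | 2(1 − r) |

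Ratio of test statistics, main effect to baseline-adjusted: 0.5·√(1 − r²)/√((1 + r)/2) = √((1 − r)/2).

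Ratio, main effect to group-by-time: 0.5·√(2(1 − r))/√((1 + r)/2) = √((1 − r)/(1 + r)).

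**Step 3: power.** A reference test with 80% power has an expected statistic of 1.960 + 0.842 = 2.802. Power of the main effect is Φ(2.802 × ratio − 1.960).

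| r | Ratio to baseline-adjusted | Power if that test has 80% | Ratio to group-by-time | Power if that test has 80% |
|---|---|---|---|---|
| 0 | 0.71 | 51% | 1.00 | 80% |
| 0.3 | 0.59 | 38% | 0.73 | 54% |
| 0.5 | 0.50 | 29% | 0.58 | 37% |
| 0.7 | 0.39 | 19% | 0.42 | 22% |

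**Step 4: dependence on effect size**, with 330 per group and r = 0.5.

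| Effect (SD) | Baseline-adjusted | Group-by-time | Group main effect |
|---|---|---|---|
| 0.2 | 84% | 73% | 32% |
| 0.3 | 99% | 97% | 60% |
| 0.4 | 100% | 100% | 84% |
| 0.5 | 100% | 100% | 96% |

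**The case against.** The strongest defence is that a journal article condenses its model. It never says that group is the only fixed effect, and the covariates in Table 1 are also absent from the model sentences. A fuller plan could contain time and group-by-time. That stands to this extent: a reader might infer that the authors excluded a time term, and the text is only silent. The decision term, however, is stated. Time alone would not change it. If an interaction were present, the group coefficient would become the difference at whichever time point is the reference, which under common coding is admission. Either way the stated term needs correcting.

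The second defence is that exact halving is conditional, and this stands. Equal admission means are not assured: there are 10 sites, mothers consent after their site has been randomised, and non-participants at intervention sites receive the same hospital care, so the admission score may follow some exposure. Pairs will not all be complete: "Mothers who have weaned or are not planning to breastfeed will not complete the BSES-SF". Missing discharge scores shift the weights away from one half. Feeding is a categorical outcome with six classes, so halving there is approximate at best.

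The third defence is that a reader might infer that most of the power is lost. The documents do not support that as a general statement. They give neither the correlation nor the effect size. At r = 0 the main effect loses nothing against group-by-time, and at 0.4 SD with r = 0.5 it keeps 84% power.

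**Conclusion.** The mismatch between the stated test and objectives i and ii stands, and it needs no assumed correlation. A group coefficient over stacked rows averages the admission and discharge differences.

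The size is conditional. The coefficient is about half of the discharge BSES-SF effect if admission means are equal in expectation and pairs are complete. The power loss can be large for effects near the detection limit when the correlation is about 0.3 or more, and is modest for large effects. All power figures rest on assumed correlations and ignore site clustering, so they serve to compare the analyses and do not forecast this study's power.

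This is a stated decision rule that gives a diluted answer if followed, and it should be corrected before the arms are compared.

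**What to change.** Define the effect as the between-arm difference at discharge, adjusted for the admission value. Then use one of two models for the BSES-SF:

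- model the discharge score with the admission score as covariate and group as fixed effect; or
- keep the long format, include time and group-by-time, and test group-by-time.

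In the long format, impose a common baseline mean only if the admission measurement can be taken as unaffected by the intervention and by recruitment after randomisation. Use the analogous HGLM for feeding at discharge.

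Add a NICU random effect in either case, since the section names only the subject effect. With discharge as the only outcome row, the subject effect drops out and NICU becomes the second level. In the long format, the levels are observation, mother and NICU.

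The cost is a few sentences in the Data analysis section and a revised model specification. Both measurements are already scheduled, so no new data are needed.
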